*Divided attention* will be measured using the Sky Search DT task from the TEA-Ch. This requires a test score from the SCORE task also. In the Score! Task, children are first asked to count to 10 as a screen. Then, children continuously count tones for 10 items (in which tones are separated by silent inter-stimulus intervals of variable duration between 500 and 5000 msec). Counting to 15 will be tested as a pre-requisite for this task. In Sky Search DT, children are required to complete the Score! and the Sky Search tasks simultaneously. Decrements in task performance relative to performances on isolated tasks will be computed as a measure of attention decrement under dual-task conditions.

*Working memory* will be assessed using tasks from the Automated Working Memory Assessment Visuospatial (AWMA) [66]. The AWMA is a computer administered test valid for use in children and adults (4–22 years). Children will complete two tasks tapping visuospatial short term (Dot Matrix, Block Recall) and two visuospatial working memory tasks (Mr X, Backwards Dot Matrix).

*Feedback utilisation* will be measured using the Inhibition Switching Task and scores from the NEPSY II. This task builds on the Inhibition naming task, and includes an attentional switching component, providing naming accuracy and speed scores.

*(c) Speed of information processing*

*Efficiency* and *fluency* will be calculated using specific test scores from the Word generation/fluency subtest from the NEPSY-II [108] as well as the Tower of London (TOL) task [109]. The NEPSY-II word generation/fluency task is designed for use in children 3–16 years, and provides age based scaled scores (mean = 10, SD = 3). Children will be required to rapidly name words based on semantic and phonemic (initial letter) cues.

The TOL task involves children completing 12 ‘problems’ in which they are required to rearrange three coloured balls on posts so that a new configuration corresponds to the pattern presented on a stimulus card. Normative data from Anderson et al. [110], will be used to transform raw scores into age based standard scores (mean = 100, SD = 15). Efficiency will be calculated using the TOL move accuracy ratio.

Fluency will be calculated using the total number of words generated in the NEPSY-II word generation task (including errors).

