Basic *speed of processing* will be measured using the processing speed index, calculated from the WISC-IV. In order to provide a measure of processing speed independent of fine motor function, the Speeded Naming task from the Neuropsychology Assessment for Children-II (NEPSY-II) [108] will also be used.

*(d) Goal setting*

Goal setting includes a number of sub components. Initiative is the ability to develop new concepts, measured by the total number of correct words in the word generation/fluency subtest from the NEPSY-II [108]. The total time required to plan the first move on the TOL provides a measure of planning, using additional process scores calculated according to guidelines provided by Anderson et al. [110]. The TOL total correct provides a measure of strategic organisation. The Rey Complex Figure Test (RCFT) assesses a child’s ability to strategically organise their response to a complex problem. Strategic organisation scores will be calculated as per Anderson et al. [111].

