### Statistical considerations

Data entry will be undertaken by the Chief Investigators (BH, CI) and research assistants. All statistical analyses will be led by a biostatistician and the Chief Investigators in consultation with the research team. Stata Statistical Software version 15 will be used for analysis. Statistics will be reported with 95% confidence interval, where appropriate, and 5% level of significance will be used.

Data will be analysed using structural equation modelling (SEM). Given the complexity of the model, confirmatory factor analysis (CFA) will be initially conducted on the four elements of EF (cognitive flexibility, goal setting, attention control and information processing) to ensure that three or four chosen measures of each element correlate well and measure the selected element. Regression based-factor scores from the CFA will then be used in the subsequent SEM that incorporates the variables in the model, presented in Fig. 1. The SEM will be used to examine the direct and indirect relationships among between EF (estimated using the BRIEF questionnaire and also the latent variable estimated using the four elements of EF). The model will be adjusted for child characteristics, unimanual capacity and intellectual functioning. For both CFA and SEM, goodness of fit of the final models will be assessed using the chi-square test statistic and goodness of fit indices, particularly the Root Mean Square Error of Approximation (RMSEA), goodness-of-fit index (GFI), Tacker-Lewis index (TLI) and the comparative fit index (CFI). Low levels of missing data are anticipated therefore no missing data imputation is planned and the analyses will explore the appropriateness of using the either maximum likelihood (ml) or maximum likelihood with missing values (mlmv) estimators.

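### One word-generation subtest supplies near-duplicate indicators to two executive-function domains, which would inflate their correlation in a joint CFA

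*Protocol article*

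**What the plan says.** Under Cognitive outcomes, part (c), Speed of information processing, fluency is scored from word generation: "Fluency will be calculated using the total number of words generated in the NEPSY-II word generation task (including errors"). The Tower of London (TOL) supplies another score: "Efficiency will be calculated using the TOL move accuracy ratio". The WISC-IV processing speed index and NEPSY-II Speeded Naming complete this domain.

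Under part (d), Goal setting, initiative is "measured by the total number of correct words in the word generation/fluency subtest from the NEPSY-II". Two further TOL scores are used: "The total time required to plan the first move on the TOL provides a measure of planning", and "The TOL total correct provides a measure of strategic organisation". The Rey figure (RCFT) adds a score for how children "strategically organise their response to a complex problem".

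Elsewhere in the same section, NEPSY-II Inhibition is placed under attention control and Inhibition-Switching under cognitive flexibility.

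Statistical considerations plans a CFA on the four elements, to check that "three or four chosen measures of each element correlate well and measure the selected element". Regression-based factor scores then enter the structural equation model. The text mentions no residual covariances or cross-loadings, and does not say whether the four elements are fitted in one model or one at a time.

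**The concern.** A factor model with independent residuals attributes every correlation between indicators of different factors to the correlation between those factors. Total and correct words come from the same performance, and one contains the other. Their shared variance is therefore mostly arithmetic and says little about how information processing relates to goal setting. A joint model has nowhere to put it except the factor correlation, and the fit improves if both factors move towards word generation.

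The secondary aim and hypothesis ask which EF sub-domains relate to bimanual performance, and the latent EF variable is built from the four elements. Both need factors that can be told apart.

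TOL also feeds both domains, and the two Inhibition tasks span two other domains. Those are distinct scores from a shared test, so they raise a weaker, shared-method version of the problem.

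**Working it through.** The article gives no figure on this point, so there is none to reproduce. It also gives no SDs, loadings or factor correlations; all such values below are assumptions shown as ranges.

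**Step 1: how close are the two word scores?** Let C be correct words, E errors and T = C + E. Let k = SD(E)/SD(C) and ρ = corr(E, C). Then

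corr(T, C) = (1 + ρk) / √(1 + k² + 2ρk).

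- k = 0.3: ρ = −0.3 gives 0.91/√0.91 = 0.95; ρ = 0.3 gives 1.09/√1.27 = 0.97.
- k = 0.5: ρ = −0.3 gives 0.85/√0.95 = 0.87; ρ = 0.3 gives 1.15/√1.55 = 0.92.
- k = 1.0: ρ = −0.3 gives 0.70/√1.40 = 0.59; ρ = 0.3 gives 1.30/√2.60 = 0.81.

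The scores are near-duplicates unless errors vary almost as much as correct words.

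**Step 2: joint CFA, independent residuals.** Four indicators per factor, as listed in parts (c) and (d), give 36 moments and 17 parameters, so 19 df. All indicators are standardised. The non-word indicators load λ on their own factor, and the true factor correlation is φ. Each word score relates equally to both domains, correlating λ²(1 + φ)/2 with every other indicator. The two word scores correlate r. Maximum-likelihood fits to the population matrix with φ = 0.5 give:

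| λ | r | estimated φ | word loadings | other loadings | RMSEA |
|---|---|---|---|---|---|
| 0.5 | 0.90 | 1.02 | 0.94 | 0.21 | 0.12 |
| 0.6 | 0.80 | 1.04 | 0.87 | 0.34 | 0.16 |
| 0.6 | 0.90 | 1.02 | 0.94 | 0.30 | 0.17 |
| 0.7 | 0.70 | 0.72 | 0.63 | 0.66 | 0.16 |
| 0.7 | 0.90 | 1.02 | 0.94 | 0.42 | 0.21 |

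Over φ = 0.3 to 0.7 and r = 0.70 to 0.98, loadings of 0.5 to 0.6 give an estimated correlation of 1.00 to 1.10. Word loadings are 0.76 to 0.99, other loadings 0.17 to 0.47, and RMSEA 0.11 to 0.17.

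At λ = 0.7 and φ = 0.3 the result is less clear. A solution at 0.47 to 0.51 exists, inflated but not collapsed. On refitting from several starting values, for r = 0.80 to 0.95 a second solution at 0.99 to 1.00 fitted better (at r = 0.90, RMSEA 0.23 against 0.29).

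If instead each word score relates only to its own domain and the overlap sits in the residuals (λ = 0.6, φ = 0.5, r = 0.80 to 0.90), the estimate is 0.80 to 0.90. Word loadings are then about 1.0, other loadings 0.36, and RMSEA 0.20 to 0.32.

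**Step 3: separate one-factor CFAs.** With λ = 0.6 and φ = 0.5, the correlation between the two regression factor scores rises from 0.41 without the excess word-score correlation to 0.44 to 0.45 with it. Over all scenarios the rise is 0.01 to 0.08.

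**Step 4: which repair works?** Take λ = 0.6 and a true φ of 0.5.

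- Residual covariance for the word pair: recovers 0.50 if the overlap is purely residual, but gives 0.83 to 0.99 (r = 0.80 to 0.98) if word generation relates to both domains.
- Correct words dropped, total words kept under information processing (refitted with seven indicators): 0.50 in the first case and 0.58 in the second, with loadings of 0.51 to 0.60.

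**The case against.** The strongest reply is that the stated purpose of the CFA reads at least as naturally as a check within each element. On that reading Step 3 applies and the harm is small. This stands, and it is why the result is conditional.

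Second, the planned fit indices would usually expose the joint misfit. At λ = 0.6, r = 0.90 and 131 children, the expected chi-square is about 19 + 130 × 19 × 0.166² = 87 on 19 df. This also stands. But the text gives no rule for respecifying a failed model, so the repair would be chosen after seeing the data.

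Third, the article deliberately separates output, including errors, from correct idea generation. As a choice of construct that is legitimate, and counting errors within fluency is not an error. It does not remove the arithmetic tie between the scores.

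Fourth, residual covariances are details that an article may leave to a fuller plan, and Fig. 1, not available here, may settle which measures enter. The assignment of scores to domains, however, is stated in the article itself.

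Two stronger inferences fail:

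- A reader might add Sky Search, because the dual-task score is a decrement: "Decrements in task performance relative to performances on isolated tasks will be computed as a measure of attention decrement under dual-task conditions". That links attention control with cognitive flexibility, so it cannot help merge information processing with goal setting. The size and sign of any built-in correlation depend on how the decrement is defined.
- A reader might see a contradiction between the two attention-control tasks and the three or four measures per element. The text counts measures, not tasks, and two tasks can yield several scores.

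**Conclusion.** The point holds in conditional form, at moderate severity. One subtest indicates two domains through scores that correlate at about 0.87 to 0.97 under the assumed error spread. In a joint CFA with independent residuals, the correlation between information processing and goal setting is inflated, often to about 1 at loadings of 0.5 to 0.6, and the other indicators lose weight. Under separate CFAs the effect is small.

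It is tempting to say that the plan as written collapses the two domains into one fluency score, or that the sub-domain question cannot be answered. The documents do not support that. They do not commit to a joint model, and the outcome depends on loadings and correlations that they do not give. Nor is the primary EF measure affected, because the BRIEF General Executive Composite uses none of these scores. The exposure is confined to the secondary sub-domain aim and the latent EF variable. The calculations cover only the word-generation overlap; the TOL and Inhibition overlaps were not sized.

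**What to change.** 1. Use word generation in one domain only. For example, drop correct words from goal setting, which keeps TOL planning time, TOL total correct and RCFT. Dropping total words from information processing is equally workable and leaves the TOL ratio, the processing speed index and Speeded Naming. The choice should follow the construct and be made before the factor models are fitted.
2. Pre-specify residual covariances for the remaining same-test pairs across domains: the TOL ratio with TOL planning time and TOL total correct, and Inhibition with Inhibition-Switching. For the word pair, a residual covariance alone is not reliable enough, as Step 4 shows.
3. State whether the CFA is one joint model or one per element.

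The cost is one indicator fewer in one domain and a few extra parameters. No new data are needed.

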##### *Secondary*

**General intellectual ability**

General intelligence will be assessed using the Wechsler Intelligence Scale for Children (4th Ed) (WISC-IV) [112]. The test comprises of ten core (and five supplemental) subtests used to calculate the FSIQ. It is valid for children aged 6–16 years. Verbal comprehension (VC), perceptual reasoning index (PRI), working memory and processing speed will be calculated as per the WISC-IV manual. Index scores have a mean = 100 and standard deviation = 15. If children are unable to complete subtests due to fine motor impairment, language impairment or reduced general ability, a composite score will be calculated [113]. For children with insufficient skills to complete subtests comprising the VC or PRI index, the alternative index will be used, so as not to disadvantage children with varying motor/language profiles. Where insufficient subtests are available, the index-based seven subtest short form score will be calculated [114]. For children unable to complete sufficient subtests to calculate a VC or PRI, this will be interpreted as profound intellectual disability, an IQ standard score of −4 standard deviation (SD) will be assigned.

*Functional attention* in daily tasks will be measured using the Conners 3rd Edition [115], a 99-item rating scale of attention related behaviours, valid for children aged 6–18 years. Age-referenced T-scores are provided (mean = 50, SD = 10). It has a large representative normative sample and is strongly connected to the Diagnostic and Statistical Manual of Mental Disorders-IV diagnostic criteria for attention disorders.

#### Neuropathology

We will obtain consent from participants’ parents/guardians to access existing brain magnetic resonance imaging (MRI) scans if they are available. Scans taken before the age of 18 months will only be included if the type of pathology was obvious and more recent imaging was not expected to provide further information. Two highly experienced paediatric radiologists (MD, JB) will assess the images to document the location, type and severity of brain injury according to the method developed by Leonard and colleagues [116, 117].

### Statistical considerations

Data entry will be undertaken by the Chief Investigators (BH, CI) and research assistants. All statistical analyses will be led by a biostatistician and the Chief Investigators in consultation with the research team. Stata Statistical Software version 15 will be used for analysis. Statistics will be reported with 95% confidence interval, where appropriate, and 5% level of significance will be used.

Data will be analysed using structural equation modelling (SEM). Given the complexity of the model, confirmatory factor analysis (CFA) will be initially conducted on the four elements of EF (cognitive flexibility, goal setting, attention control and information processing) to ensure that three or four chosen measures of each element correlate well and measure the selected element. Regression based-factor scores from the CFA will then be used in the subsequent SEM that incorporates the variables in the model, presented in Fig. 1. The SEM will be used to examine the direct and indirect relationships among between EF (estimated using the BRIEF questionnaire and also the latent variable estimated using the four elements of EF). The model will be adjusted for child characteristics, unimanual capacity and intellectual functioning. For both CFA and SEM, goodness of fit of the final models will be assessed using the chi-square test statistic and goodness of fit indices, particularly the Root Mean Square Error of Approximation (RMSEA), goodness-of-fit index (GFI), Tacker-Lewis index (TLI) and the comparative fit index (CFI). Low levels of missing data are anticipated therefore no missing data imputation is planned and the analyses will explore the appropriateness of using the either maximum likelihood (ml) or maximum likelihood with missing values (mlmv) estimators.

## Discussion

This study protocol reports a prospective, multi-centre, cross-sectional study that will provide new knowledge of the multiple and concurrent processes that contribute to task performance in children with unilateral CP. Cognition and bimanual performance are both factors known to affect functional outcomes but have not yet been studied concurrently. Knowledge from this study has the capacity to significantly influence, inform and adapt clinical practice. It is anticipated that distinct profiles of motor, cognitive and neuropathology will be identified. This understanding will improve the specificity and targeting of existing upper limb interventions. It may also lead to the development of novel methods to improve cognitive and motor outcomes in children with unilateral CP. Dissemination of results and translation of knowledge into clinical practice will begin immediately via professional development opportunities provided by site investigators. The large number of university affiliations across the study team also provides opportunities to integrate learning into undergraduate education. Knowledge translation strategies will also target parents and teachers of children with CP.

## Abbreviations

AHA: Assisting Hand Assessment
AWMA: Automated Working Memory Assessment
BRIEF: The Behaviour Rating Inventory of Executive Function
CFCS: Communication Function Classification System
CO-OP: Cognitive Orientation to daily Occupational Performance
CP: Cerebral Palsy
CQ: Cognitive Quotient
DCD: Developmental Coordination Disorder
EF: Executive Functioning
FSIQ: Full-Scale Intellectual Quotient
GMFCS: Gross Motor Function Classification System
ICC: Intraclass correlation coefficient
ID: Intellectual Disability
IQ: Intellectual Quotient
MACS: Manual Ability Classification System
MRI: Magnetic Resonance Imaging
NEPSY-II: Neuropsychology Assessment for Children-II
PAIS: Perinatal Arterial Ischaemic Stroke
PRI: Perceptual Reasoning Index
PVHI: Periventricular Haemorrhagic Infarction
PVL: Periventricular White Matter damage
SD: Standard Deviation
TEA-Ch: Test of Everyday Attention for Children
TOL: Tower of London
VC: Verbal Comprehension
WISC-IV: Wechsler Intelligence Scale for Children 4th Edition
